### Outcome Measures

The primary outcome measure is the proportion of participants attaining a change in the weight-for-age *Z* score (WAZ) by ≥0.5, as per WHO reference standards, from baseline to weeks 12 and 16. The secondary outcome measures include changes in anthropometric measurements (weight in kg, height in cm, and midupper arm circumference in cm), which will be assessed every 2 weeks for 12 weeks, followed by assessment at week 16. Change in the frequency of illnesses will be assessed at baseline, week 12, and week 16 using a predesigned table that records the frequency and duration of illnesses. Assessment of safety (complete blood count [CBC], liver function test [LFT], renal function test [RFT], and serum electrolytes) will also be performed at baseline and week 12 in a small proportion of participants whose parents provide consent.

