### Sample Size

The sample size for the study has been calculated assuming that 60% of participants in the intervention arm and 30% of participants in the control arm will achieve a change in *Z* score of ≥0.5 according to the WHO weight-for-age growth standards. With a 95% CI and 80% power, 42 participants per group need to be enrolled in the trial. After accounting for an attrition rate of 20%, the sample size for the study has been finalized as 50 per group. Therefore, a total of 100 participants per center will be enrolled in the trial.

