#### Follow-Up Assessments

All participants will undergo follow-up assessments on days 14, 28, 42, 56, 70, 84, and 112. Concomitant medication, rescue medication, drug compliance, and adverse drug reactions or adverse drug events will be assessed during the follow-up visits. Laboratory investigations will be performed at the day 84 visit for those who underwent baseline laboratory assessments (Table 1).

**Table 1 table1:** Study schedule.

Assessments	Screening or baseline	Follow-up		
		Weeks 2-10 (days 14, 28, 42, 56, and 70)	Week 12 (day 84)	Week 16 (day 112)
Informed consent from parent	✓			
Laboratory investigations (for those who are willing)	✓		✓	
Demographic characteristics and medical history	✓			
Weight-for-age *Z* score	✓		✓	✓
Anthropometric measurements (weight, height, midupper arm circumference, and BMI)	✓	✓	✓	✓
Assessment of illness frequency	✓		✓	✓
*Dosha*, *dhatu*, and *srotopareeksha* assessment	✓			
Assessment of concomitant medications		✓	✓	✓
Assessment of rescue medications		✓	✓	✓
Assessment of adverse drug reactions and adverse events		✓	✓	✓
Drug compliance assessment		✓	✓	
Dispensing of trial drug and compliance reporting form	✓	✓		

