### Participant Withdrawal Guidelines

Participants will be withdrawn from the trial if they experience a serious adverse event, regardless of whether it is related to the trial drug or if they experience an adverse drug reaction that requires discontinuation of the trial medication. Acute illness requiring inpatient treatment during the study period, worsening of the existing condition, voluntary withdrawal from the study by parents, and drug compliance of less than 80% will also result in withdrawal from the study. The reason for withdrawal will be documented in the CRF, dated, and signed. Participants withdrawn from the trial will undergo a final examination if possible. If participants leave against medical advice, a final telephone interview will be conducted with the parents to assess the participant’s health status from the point of view of drug safety and the validity of study results.

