### Statistical Methods

The primary outcome of the study, namely, the proportion of participants achieving an improvement in the WAZ of ≥0.5, will be analyzed using an intention-to-treat approach. Between-group comparisons for the primary binary outcome will be performed initially using the chi-square test, followed by multivariate logistic regression to estimate adjusted effect sizes after controlling for important covariates, including study center, baseline, WAZ, age, sex, and other clinically relevant variables. This will be done in the following steps:

Step 1: an unadjusted between-group comparison will be performed using the chi-square test to examine the crude difference in the proportion of participants achieving the primary outcome between the intervention and control groups. This provides transparency and allows readers to evaluate the raw effect.Step 2: multivariate logistic regression will be used to estimate the adjusted odds ratio and 95% CI, while controlling for the following prespecified covariates: study center, baseline WAZ (continuous), age (months), sex, baseline nutritional status category, socioeconomic status, and educational status of parents. The adjusted analysis represents the primary analytic result and will be emphasized in reporting and interpretation.

For the secondary outcomes, within-group pre-post changes will be examined using a paired *t* test or Wilcoxon signed-rank test, as appropriate, and will be reported for descriptive purposes. For parameters assessed at multiple follow-up time points, repeated-measures ANOVA or the Friedman test will be applied to assess temporal trends. All analyses will be performed using SPSS (version 29.0; IBM Corp), and statistical significance will be assessed at α=.05 (2-tailed).

Participants who withdraw, are lost to follow-up, or do not complete the week 12 assessment will be documented, and reasons for dropout will be recorded. Dropout rates and reasons will be presented by study group in the CONSORT (Consolidated Standards of Reporting Trials) flowchart.

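### The named trend tests for weight, height and midupper arm circumference use only children with all eight measurements, so the visits of children who withdraw are discarded and the trends may be biased

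*Protocol article*

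**What the plan says.** Under Statistical Methods, the article divides the secondary analyses in two. Within-group pre-post changes get a paired t test or Wilcoxon signed-rank test. Repeatedly measured outcomes get the following: "For parameters assessed at multiple follow-up time points, repeated-measures ANOVA or the Friedman test will be applied to assess temporal trends". The software is SPSS 29.0.

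Outcome Measures gives the schedule for weight, height and midupper arm circumference: "which will be assessed every 2 weeks for 12 weeks, followed by assessment at week 16". Follow-Up Assessments gives the days: "All participants will undergo follow-up assessments on days 14, 28, 42, 56, 70, 84, and 112". With baseline, that makes eight occasions.

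Two other sections bear on how many children will have all eight values:

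- Sample Size: "After accounting for an attrition rate of 20%, the sample size for the study has been finalized as 50 per group".
- Participant Withdrawal Guidelines: serious adverse events lead to withdrawal whatever their cause, and so do "Acute illness requiring inpatient treatment during the study period, worsening of the existing condition, voluntary withdrawal from the study by parents, and drug compliance" under 80%. A withdrawn child has a final examination where possible. The section does not say that scheduled visits continue.

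The intention-to-treat approach is stated for the primary outcome.

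**The concern.** Repeated-measures ANOVA as usually run, and the Friedman test, work on a rectangular table with one row per child and one column per visit. A child with an empty cell leaves the analysis altogether, and the readings already taken leave too. The protocol pairs these tests with an eight-visit schedule, a stated attrition allowance and compulsory withdrawal for several reasons.

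Two things are at stake. The first is waste: a child measured five or six times contributes nothing to the trend. The second is selection. Worsening of the existing condition means, in this trial, worsening undernutrition, so that withdrawal rule acts on or close to the outcome. Inpatient illness and serious adverse events may also go with poor growth.

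Losses may also differ between arms. The trial is open, so parents know the allocation. Controls take no trial medicine after week 4, so new low-compliance withdrawals in weeks 5 to 12 would be expected in the study arm.

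The Discussion counts evaluation of trends over time among the study's strengths, so these analyses are meant to be read.

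**Working it through.** **Inputs from the article.** 200 children, 1:1; eight occasions; 20% attrition allowance; 42 per group before attrition and 50 after; 60% against 30% responders; 80% power; two-sided 5% level.

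**1. The plan's own figure.** With pooled variance under the null:

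n = [1.960 × √(2 × 0.45 × 0.55) + 0.842 × √(0.6 × 0.4 + 0.3 × 0.7)]² / 0.30² = (1.379 + 0.565)² / 0.09 ≈ 42 per group.

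This reproduces the stated 42. The step to 50 is looser: 42/0.80 gives 53 and 42 × 1.20 gives 51, while 1 − 42/50 = 16%. I use the stated 20% and give 16% as the alternative.

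**2. Children lost if completers miss no visit.**

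- At 20%: 200 × 0.20 = 40 lost, 160 kept.
- At 16%: 200 × 0.16 = 32 lost, 168 kept.

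**3. Adding single missed visits.** A child who reaches day 112 can still miss any of six intermediate follow-ups (days 14 to 84). With an assumed miss probability m at each, independent across visits, the share kept is 0.80 × (1 − m)⁶.

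| m (assumed) | Share kept | Children of 200 |
|---|---|---|
| 0 | 80% | 160 |
| 1% | 75% | 151 |
| 3% | 67% | 133 |
| 5% | 59% | 118 |

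**4. Readings discarded.** Assume the first missed visit is spread evenly over the seven follow-ups. A dropout then has on average four readings, counting baseline. Per outcome, 40 × 4 = 160 readings are discarded out of 160 × 8 + 160 = 1,440 recorded, or 11%.

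**5. Bias.** With dropout share d, completers' mean gain minus the mean gain of all children equals d × (completer gain − dropout gain). At d = 0.20:

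- dropouts gain 0.2 kg less: +0.04 kg
- no difference: 0
- dropouts gain 0.2 kg more: −0.04 kg

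A simulation with assumed growth (mean 0.04 kg per week, between-child SD 0.03, measurement SD 0.1 kg) and 20% dropout gave these week-16 gains:

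| Who leaves | Completers | All children |
|---|---|---|
| At random | 0.637 kg | 0.638 kg |
| Mostly poor growers | 0.715 kg | 0.641 kg |
| Mostly good growers | 0.567 kg | 0.641 kg |

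**6. What a likelihood analysis of all visits recovers.** A second simulation assumed 100 children per arm, a true day-84 gain of 0.60 kg, between-child SD 0.3 to 0.5 kg, measurement SD 0.12 kg and 20% dropout, with the last visit between days 28 and 84. Selective dropouts came from the third with the lowest true growth rate.

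| Dropouts from slowest third | Completers | All observed visits |
|---|---|---|
| Half of them | 0.64–0.66 kg | about 0.61 kg |
| All of them | about 0.68–0.73 kg | about 0.61–0.62 kg |

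Most of the bias goes, but not all, because here dropout depends on true growth, which the visits show only in part.

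**The case against.** A reader might infer from the withdrawal rules that the trends are certain to be biased upward in both arms. The documents do not support that. They give reasons for withdrawal but no frequencies, parental withdrawal and low compliance have no stated link to growth, and step 5 shows that the bias can be zero or negative.

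Four further objections deserve weight.

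- **Imputation may be planned elsewhere.** The article is condensed and any analysis plan is not shown. If missing values are imputed first, rows are not deleted. This stands as a condition. The point therefore rests on the tests that are named, not on any absence of missing-data text.
- **Not every secondary result is affected.** The paired tests need two values, so a child who misses day 42 still counts for the change to week 12. Nothing confines descriptive visit means to complete rows. This stands.
- **The 20% is a planning allowance, not a forecast,** and the step from 42 to 50 covers only 16%. This also stands. At 16% the loss is 32 children, and the argument is the same.
- **The consequence is limited.** This is a pilot with secondary trend tests, and no treatment comparison is stated for them. That limits the weight of the point. The deletion would occur whether or not arm were added as a factor, so it is separate from the question of a between-arm test.

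**Conclusion.** The point holds in a limited form. The article names two tests that, without imputation, use complete rows only, for outcomes with eight occasions and an acknowledged allowance for attrition. About 40 of 200 children (32 if attrition is 16%) would be left out of the trend analysis of weight, height and midupper arm circumference. The analysable share would fall to between 75% and 59% under assumed miss rates of 1% to 5% per intermediate visit. The 11% of readings discarded depends on dropout being evenly spread.

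The trends may be biased, plausibly upward given the withdrawal rules. The kilogram figures are illustrations under assumed growth and dropout and are not estimates for this trial. The primary binary analysis and the two-point paired tests are not touched by this deletion rule. It is an inexpensive improvement to a secondary analysis and does not threaten the trial's main result.

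**What to change.** In Statistical Methods, for weight, height and midupper arm circumference, replace repeated-measures ANOVA and the Friedman test with a linear mixed model for repeated measures. Suggested wording:

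> Weight, height and midupper arm circumference at the seven follow-up visits will each be analysed with a linear mixed model including arm, visit (categorical), arm-by-visit interaction, baseline value and centre, with an unstructured covariance matrix across visits. Every randomised child with a baseline and at least one post-baseline measurement will be included, and all visits up to withdrawal will contribute.

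If dropout is evenly spread as in step 4, about 40/7 ≈ 6 children would leave before day 14 and have no post-baseline value. The model would then keep about 194 children where the named tests keep 160.

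**Cost.** The MIXED procedure in the named SPSS version fits this model, and no new data, visits or children are needed. Enrolment is complete, so the change should go through the protocol's own amendment route, with ethics committee approval, before the data are analysed.

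**Downside.** The model assumes data are missing at random given the observed visits. It reduces bias from dropout related to recorded growth but cannot eliminate bias from unobserved reasons, and the report should say so.

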### Data Monitoring

CCRAS, the trial’s sponsor and coordinating center, will conduct periodic site monitoring through a committee of experts and a biostatistician to ensure compliance with Good Clinical Practice and the study protocol.

### Ethical Considerations

The IEC at National Ayurveda Research Institute for Panchakarma, Cheruthuruthy (F.No. 8/16/2023/NARIP/Tech meeting/2506; March 31, 2023), and the IEC at Maharao Shekhaji Regional Ayurveda Research Institute, Jaipur (F.5/Lab/Project/Ethics/2007-08CRAI-JPR/Part-1/455; May 3, 2023), approved this study. The trial was prospectively registered with the Clinical Trials Registry of India (CTRI/2023/07/055188) on July 13, 2023. This trial is conducted in accordance with the Declaration of Helsinki, the Indian Council of Medical Research guidelines 2017, and CCRAS Research Policy. Informed consent will be obtained from parents by the investigators before trial participation, ensuring that the parents’ right to autonomy is upheld. Participant confidentiality will be maintained throughout all phases of the study, with access to data granted only to study personnel, sponsors, and the monitoring team. The IEC has approved the study protocol and the written informed consent form, ensuring the confidentiality and privacy of participants’ personal and medical information.

## Results

The study received funding in March 2023. Participant enrolment commenced on December 16, 2023 and has been completed. The study is ongoing at 2 CCRAS centers. After data analysis, the study findings are expected to be submitted for publication in December 2026.

## Discussion

### Anticipated Findings

Malnutrition stunts the growth and potential of children, ultimately hindering a nation’s economic progress and prosperity. Reinforcing public health interventions in children aged <5 years, facilitating early diagnosis, ensuring effective implementation, and evaluating strategies and measures aimed at socioeconomic development are imperative for the successful management of children aged <5 years’ malnutrition in India [2]. A recent study revealed that mild underweight variability has a stronger association with child mortality rates than severe underweight variability [13]. Hence, mild to moderate malnutrition should not be overlooked, and its management should be prioritized to prevent long-term consequences.

Most conventional strategies emphasize nutritional rehabilitation primarily through supplementation. However, they may not adequately address the underlying digestive and metabolic disturbances that can limit nutrient use [14]. Emerging evidence from gut microbiome research shows that malnourished children often have immature or dysbiotic gut microbiota [15]. Additionally, dietary patterns in children significantly influence gut microbiome composition, thereby affecting nutrient metabolism and energy harvest [16,17]. Conventional supplements do not help restore a healthy gut microbiota, potentially limiting long-term recovery from malnutrition. This protocol addresses this gap by incorporating an initial phase of digestive correction before the initiation of nourishing therapy. According to Ayurveda, every disease originates from weak digestive power. Malnutrition in children is correlated with *Kumarasosha* a condition resulting from various faulty dietary etiologies affecting digestion. These etiologies include undernutrition, the consumption of junk foods, and incompatible diets. Such practices, if continued, primarily weaken digestion and lead to the formation of toxic metabolites (*ama*), which accumulate in the body channels, obstruct them, and affect tissue transformation. At this juncture, if nourishing drugs or dietary interventions are administered, they can lead to improper digestion, which may further weaken digestion and increase the accumulation of *ama*, thereby obstructing the channels and perpetuating this vicious cycle. Ayurveda emphasizes the primary correction of digestive fire (*agni*) and the clearance of toxic metabolites and channel obstructions before starting nourishing therapy. This first line of management is essential for creating a suitable platform for nourishing therapy. The second line of management is nourishing therapy itself.

The *Kashyapa Samhita*, a classical textbook of Ayurvedic pediatrics, defines “Lehana” as a formulation that is heavy to digest but nourishing and is recommended for emaciated children [18]. *Ayush-BR Leham*, the trial drug, is one such nutritional supplement. The nutrition supplied after digestion correction is expected to be properly digested and assimilated by the body, supporting healthy weight gain [19]. Studies support that intestinal dysfunction, inflammation, and environmental enteric dysfunction can impair nutrient absorption despite adequate intake from fortified foods [20]. Hence, the sequential treatment approach is conceptually robust, as it aims to optimize digestive and metabolic functions before nutritional supplementation, thereby enhancing nutrient bioavailability and assimilation [21]. Such a strategy is likely to promote more effective and sustained recovery, rather than transient weight gain alone. This study design thus offers more treatment responsiveness and reduces the likelihood of incomplete recovery observed in standard supplementation-based interventions.

This study is designed as an exploratory randomized controlled trial to evaluate the efficacy of the nutritional supplement, *Ayush-BR Leham*, in moderately malnourished children. It is hypothesized that the trial intervention will result in a clinically meaningful improvement in nutritional status, reflected by an increase of ≥0.5 in WAZ among moderately malnourished children. Additionally, the intervention is expected to improve anthropometric parameters and reduce illness frequency compared with the control group.

The study has several strengths, including a randomized controlled design, the use of standardized and clinically relevant outcome measures such as WAZ, and repeated follow-up assessments that enable evaluation of trends over time. WAZ is a well-established indicator of child mortality and is sensitive to changes associated with nutritional interventions. Previous trials have demonstrated that improvements in WAZ reflect meaningful recovery and improved clinical outcomes [22,23]. Even mild improvements in WAZ following a short-term intervention with a nutritional supplement signify a positive shift in overall nutritional status and reduced morbidity. Additionally, a *Z* score ≥0.5 exceeds the normal day-to-day variation expected due to fluctuations in hydration status, illness, or measurement errors [24].

The intervention is based on a rational approach that addresses both nutritional deficiency and the underlying pathology, adding novelty to the study. However, the design does not permit complete isolation of the independent effects of the intervention components due to the initial common treatment phase. Although both groups are advised to follow a home-prepared diet, variations in dietary composition, quantity, and adherence at the household level may introduce residual confounding. However, the randomized design is expected to distribute such dietary variations equally between groups, thereby minimizing their impact on the comparative outcome. Despite these limitations, the study is expected to generate preliminary evidence to inform larger confirmatory studies across diverse geographic and socioeconomic settings, thereby enhancing external validity. Implementation research exploring its feasibility within community-based platforms, such as Integrated Child Development Services and *Poshan Abhiyan*, could support policy-level adoption if efficacy is established.

### Future Prospects

*Ayush-BR Leham* is expected to improve the WAZ (WHO), anthropometric measurements, and the frequency of illness. The trial is anticipated to yield crucial data on the efficacy and safety of this nutritional supplement. The results of this study may give scientific insights for the development of strategies to manage moderate malnutrition in children. If the intervention is found to be effective, the findings may help in the incorporation of Ayurvedic guidelines into standard treatment protocols for children with moderate malnutrition.

## Appendix

Multimedia Appendix 1 Peer-reviewer report from the Project Evaluation Monitoring Committee, Central Council for Research in Ayurvedic Sciences, Ministry of Ayush, Government of India.

## Abbreviations

BR: Bala Rakshak
CBC: complete blood count
CCRAS: Central Council for Research in Ayurvedic Sciences
CONSORT: Consolidated Standards of Reporting Trials
CRF: case report form
IEC: institutional ethics committee
LFT: liver function test
RFT: renal function test
SPIRIT: Standard Protocol Items: Recommendations for Interventional Trials
WAZ: weight-for-age Z score
WHO: World Health Organization
